**FIGURE 1 eph13343-fig-0001:**
[figure not shown]
Schedule of enrolment, interventions and assessments. Abbreviations: CPM, conditioned pain modulation; EIH, exercise‐induced hypoalgesia; GPAQ, global physical activity questionnaire; NDI, neck disability index; PCS, pain catastrophizing scale; SF‐36, 36‐item short form survey; ‐t_1_, enrolment week 0; t_0_, allocation; t_1–2_, intervention, baseline and post‐intervention assessments; TS, temporal summation; TSK, Tampa scale of kinesiophobia.

This study is a randomized crossover trial, in which all participants will take part in all interventions, but the order in which they are assigned to the interventions is randomized. Participants will attend the first data collection session, during which baseline questionnaires and physical assessments will be measured, followed by the intervention, and a post‐intervention physical assessment will be measured. There will be a 1‐ to 2‐week washout period before the second data collection session, which is identical to the first session minus the baseline questionnaires, with a different intensity of intervention.

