### Data collection

2.6

Demographics, including age, sex, education level, duration of chronic NP, physical activity participation level (GPAQ; Cleland et al., 2014) and employment status, will be collected. The outcome assessments consist of questionnaires and central pain processing measurements. Questionnaires will be assessed at the start of each exercise session, and the central pain processing measurements will be performed twice at each session: at baseline; and postexercise.

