### Sample size

2.8

For this clinical trial, the sample size is calculated based on PPT. Calculations for an appropriate sample size were performed with G*Power (v.3.1.9.6; Dusseldorf, Germany) (Faul et al., 2007). Given that there are no data on aerobic exercise testing with similar intervention groupings in chronic NP, the a priori power analysis was conducted based on data from an exercise intervention study with similar intervention grouping (Taimela et al., 2000). The sample size of this study is calculated based on the difference in mean PPTs (25.0 ± 19.7; 42.1 ± 27.2) between two different exercise interventions, a desired two‐tailed α = 0.05, β = 0.20, and an allocation ratio of 1:1. The calculations revealed that 64 participants would be sufficient. However, to allow a loss to follow‐up of 20% and taking a conservative approach, a total of 80 participants with chronic NP will be recruited.

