### Statistical analysis

2.9

All data will be analysed via scatterplots, boxplots and Kolmogorov–Smirnov statistics to evaluate normality. Normally distributed data will be reported as the means and 95% confidence interval. Other data will be reported as the median and interquartile range. Parametric tests will be used for normally distributed data, and non‐parametric tests for non‐normal distributed data, to analyse between‐group differences for physical outcome measures and baseline questionnaires and physical measures.

To test for carryover effects, the sum of the measured values in the sessions for each patient will be calculated and compared across the two groups with Student's unpaired *t*‐test (Wellek & Blettner, 2012). A *P*‐value of >0.05 indicates no carryover effects, and the ‘washout’ duration is sufficient. To determine the statistical difference between HIGH and LOW, the within‐subject difference in outcome parameters between both sessions will be calculated using Student's unpaired *t*‐test. If there is a statistical significance, a regression model will be conducted to evaluate the effect of exercise intensity (HIGH vs. LOW) on CS measures. The fixed effect of time (baseline and postexercise), exercise intensity and study group will be included in the model, with age as a covariate. If no statistical difference is detected, repeated‐measures ANOVA will be performed to assess significant differences between both groups; the within‐subject factor will be defined as ‘time’, with ‘group’ as a between‐subject factor. The significance level will be adjusted by the number of comparisons using Bonferroni correction.

Multivariate regression analysis will be used to analyse the association between [La] and EIH. In order to examine the relationship between individual measures of CS (EIH, CPM and TS), separate regressions will be conducted. Models will be adjusted for age, sex, education level, physical activity level, NDI, PCS and TSK. Statistical significance is set at *P* < 0.05.

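### No step of the HIGH–LOW comparison uses the session's own pre-exercise value as a covariate, so it is less precise than the collected data allow

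*Protocol article*

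**What the plan says.** Every participant completes both intensities: "all participants will take part in all interventions, but the order in which they are assigned to the interventions is randomized" (Setting and design, 2.2). The central pain processing measures are "performed twice at each session: at baseline; and postexercise" (Data collection, 2.6), so each person has a pre-exercise value for the HIGH day and another for the LOW day.

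Statistical analysis (2.9) then compares the intensities in stages.

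- First, "the within‐subject difference in outcome parameters between both sessions will be calculated" and examined with an unpaired t-test. No covariate is listed. The text does not say whether the outcome parameter is the postexercise value or the change from that session's baseline.
- If that test is significant, a regression follows with fixed effects for time (two levels, before and after exercise), intensity and study group, "with age as a covariate". No time-by-intensity term is named.
- If it is not significant, a repeated-measures ANOVA is run with time within subjects and group between subjects.

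The session's own pre-exercise value is not a covariate at any of these stages.

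**The concern.** Two sessions held one to two weeks apart will differ in a person's pain sensitivity for reasons unrelated to cycling. The pre-exercise measurement on each day is the direct record of that difference. If the t-test uses postexercise values, the day-to-day shift stays in the HIGH–LOW difference as noise. If it uses change scores, the whole baseline difference is subtracted, which over-corrects whenever the baseline is an imperfect predictor of the postexercise value and adds measurement error.

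The one covariate that the plan names, age, describes differences between people, and a crossover removes these by design. What is at stake is the width of the confidence interval for the primary outcomes, at a significance level that the plan also divides by Bonferroni correction.

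**Working it through.** **The plan's own figure.** Sample size (2.8) uses "the difference in mean PPTs (25.0 ± 19.7; 42.1 ± 27.2) between two different exercise interventions" with "a desired two‐tailed α = 0.05, β = 0.20, and an allocation ratio of 1:1". The pooled SD is √((19.7² + 27.2²)/2) = √563.97 = 23.75 and d = 17.1/23.75 = 0.72. For two independent groups, the noncentral t gives 31.27, hence 32 per group and 64 in total (power 0.809), which agrees with "The calculations revealed that 64 participants would be sufficient". Then 64/0.80 = 80, as stated. The figures reproduce, but as an independent-groups calculation.

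**Age.** Write each observation as a person effect (which includes any effect of age) plus session, intensity and error terms. In HIGH minus LOW for the same person, the age term subtracts out. In a simulation of the two-session crossover (64 complete participants, 4,000 runs per setting), adding age changed the estimate by less than 10⁻¹⁴ in the postexercise, main-effects and interaction models.

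**Session baseline.** Let P be the HIGH–LOW difference in postexercise values and B the HIGH–LOW difference in pre-exercise values. Assume that each has variance V, with correlation r. For any weight b given to the baseline,

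Var(P − bB) = V(1 + b² − 2br).

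- Postexercise values only (b = 0): V
- Change scores (b = 1): 2V(1 − r)
- Baseline as covariate (b = r, the minimum): V(1 − r²)

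The covariate analysis therefore has 1 − r² of the variance of the postexercise comparison and (1 + r)/2 of the variance of the change-score comparison. The documents give neither r nor the equality of variances; both are assumptions. The interval width scales with the square root.

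| r (assumed) | Variance ratio against post values | Interval width | Variance ratio against change scores | Interval width |
|---|---|---|---|---|
| 0.2 | 0.96 | 0.98 | 0.60 | 0.77 |
| 0.5 | 0.75 | 0.87 | 0.75 | 0.87 |
| 0.8 | 0.36 | 0.60 | 0.90 | 0.95 |

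At r = 0.5, either reading would need 1/0.75 = 1.33 times the participants to match the adjusted analysis.

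**Check by simulation.** Empirical standard errors at 64 participants, in arbitrary units:

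| r | Post values | Change scores | Baseline as covariate |
|---|---|---|---|
| 0.25 | 0.114 | 0.137 | 0.111 |
| 0.50 | 0.112 | 0.112 | 0.098 |
| 0.75 | 0.114 | 0.079 | 0.075 |

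All three estimators were centred on the true effect of 0.40. The covariate analysis was never the least precise, even after paying for its extra degree of freedom.

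**The regression with only the listed terms.** Without a time-by-intensity term, the intensity coefficient averages the HIGH–LOW contrast before exercise (zero) and after it: (0 + 0.40)/2 = 0.20. The simulation gave 0.20.

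**The case against.** A t-test on within-person differences, compared by sequence, is a standard and valid crossover analysis. Fine covariate detail may sit in an analysis plan that is not shown. This stands as far as validity goes. It does not remove the point, because the article itself names the covariate, and both readings of the outcome parameter are less efficient than the adjusted analysis.

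The size of the gain is uncertain, and this stands too. Exercise-induced hypoalgesia is itself a difference in pressure pain threshold around a wall-squat, and conditioned pain modulation is read against the baseline threshold from that assessment. For such outcomes r is a correlation between differences of differences and could be low. With r near zero, adjustment gains almost nothing over postexercise values, though it still halves the variance of change scores.

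Several stronger readings are tempting, but the documents do not support them.

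- *The main comparison adjusts for age instead of baseline.* It does not: the t-test has no covariate, and age enters only in the conditional regression.
- *Baseline is ignored.* It is a response level of time in the regression, and change scores would use it in part.
- *The estimate is biased by chance baseline differences.* With randomised order and no carryover, these add noise and not bias.
- *The trial is underpowered as a result.* On the plan's inputs, a paired calculation needs 33 participants at a correlation of 0 between the two conditions and 18 at 0.5, against 64 evaluable.
- *Age should be removed.* Keeping it costs essentially nothing. With incomplete pairs (the plan allows 20% attrition) or no participant effect in the model, it can alter the standard error or shift the estimate slightly.
- *The baseline is taken immediately before cycling.* Procedures (2.4) puts a 10-minute wait between them, which may lower r somewhat.

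**Conclusion.** The point holds as a matter of precision. The plan collects a pre-exercise value in each session and never uses it as a covariate when it compares HIGH with LOW. The one covariate it names does not change that contrast as a main effect in complete data.

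Under equal variances and an assumed r from 0.2 to 0.8, the variance given up lies between 4% and 64% if postexercise values are compared, and between 40% and 10% if change scores are compared. No single figure can be fixed, because the documents state neither r nor which outcome is meant. The gain matters most for temporal summation and conditioned pain modulation, which were not the basis of the sample size.

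The unnamed time-by-intensity term is a related gap in the regression. Not naming it does not show that it will be left out, but the terms as listed would not isolate the postexercise effect.

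**What to change.** State for each primary outcome whether the outcome parameter is the postexercise value. Then prespecify one analysis: the between-session difference in postexercise values, regressed on the between-session difference in pre-exercise baselines, with sequence as the group term. If differences are taken as first minus second session and sequence is coded ±1 (+1 for HIGH first), the sequence coefficient is the HIGH–LOW effect and the intercept carries the period effect.

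The equivalent mixed model has the postexercise value as response, with intensity, period, session baseline, participant-mean baseline and a participant effect. If the repeated-time form is kept, name the time-by-intensity term as the estimate of interest. Age may remain in the model.

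The data are already collected. The cost is redrafting, about one degree of freedom, and reliance on the washout that the plan already assumes, since the second session's baseline follows the first intervention. The adjusted model does not slot directly into the plan's non-parametric branch, so the redraft should also say what is done for non-normal outcomes.

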
Although the evidence indicates that exercise alters central pain modulation, it is not known whether the clinical presentation of CS is associated with the mechanistic effect of exercise on hypoalgesia. Therefore, the primary aim of this study is to investigate the immediate effect of a single bout of physical exercise on CS in individuals with chronic NP. The secondary aim is to investigate the relationship between lactate concentration ([La]), CS and pain sensitivity. With the knowledge that lactate plays an important role in the maintenance of chronic pain, we hypothesize that lactate produced during exercise will have a positive correlation with EIH. Although exercise might induce similar hypoalgesic responses across different chronic pain conditions (Polaski et al., 2019), comparing these effects across different types of chronic pain poses challenges (Rice et al., 2019). Notably, differences in the mechanisms underlying different chronic pain conditions (Bogduk, 2011; Knezevic et al., 2021; Popescu & Lee, 2020) and different management strategies and recovery trajectories have led to different clinical guidelines for different chronic pain conditions (Blanpied et al., 2017; George et al., 2021). To ensure that the findings of this trial are valid and reproducible and optimally inform clinical practice, this study focuses on chronic non‐specific NP alone in order to ensure a homogeneous population.

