### Procedures

2.4

Participants who meet the inclusion criteria will be invited to attend two testing sessions: one to perform high‐intensity submaximal aerobic bicycle exercise (HIGH); and a second to complete a low‐intensity submaximal aerobic bicycle exercise (LOW). The order of these two testing sessions will be randomized. Participants will be asked to refrain from analgesics on the day of testing and to abstain from physically demanding activities, including exercise, for 48 h before testing. Participants will also be asked to abstain from nicotine, alcohol and caffeine for 12 h before testing.

Participants will be given a detailed explanation about the research study and the requirements of them. Informed consent will be obtained from the participants before collecting any data. Figure 2 depicts the flowchart of study procedure and the assessments conducted at each assessment time point. Participants will be randomized into two main groups, termed the INV‐A group and the INV‐B group, with INV‐A doing HIGH–LOW and INV‐B doing LOW–HIGH. Participants will wait 10 min before commencing the exercise intervention to prevent a carryover effect from the baseline physical assessments influencing exercise. During the waiting time, resting heart rate (HR) and blood pressure will be measured, and appropriate warnings and precautions will be briefed. Participants will then complete the assigned exercise intervention, immediately followed by postexercise assessment. The order of testing will be kept constant within each testing session, both before and after exercise. To prevent a carryover effect, the sessions will be scheduled 1–2 weeks apart.

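### The follow-up regression for HIGH versus LOW lists no intensity-by-time term, so its intensity coefficient estimates half of the effect on the postexercise response

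*Protocol article*

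**What the plan says.** The Introduction gives the aim: "the primary aim of this study is to investigate the immediate effect of a single bout of physical exercise on CS". Under Procedures each participant attends a HIGH and a LOW session: "The order of these two testing sessions will be randomized". Under Data collection, "the central pain processing measurements will be performed twice at each session: at baseline; and postexercise". A participant who completes both sessions therefore supplies four values of each measure.

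The Statistical analysis section first assigns the comparison of HIGH with LOW to an unpaired t-test on within-subject differences between sessions. If that test is significant, "a regression model will be conducted to evaluate the effect of exercise intensity (HIGH vs. LOW) on CS measures". The terms of the regression follow: "The fixed effect of time (baseline and postexercise), exercise intensity and study group will be included in the model, with age as a covariate". No intensity-by-time term is named, the pre-exercise value is not a covariate, and the outcome is not defined as a change score. If the t-test is not significant, the plan turns to a repeated-measures ANOVA with time and group as its only factors.

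**The concern.** The question is whether the response to a bout of cycling differs between HIGH and LOW. In a model whose rows include both the pre-exercise and the postexercise values, that difference is the intensity-by-time interaction. The listed model has no such coefficient. Its intensity term compares all HIGH rows with all LOW rows, and half of those rows were recorded before anyone had cycled. Its time term gives the average response over both intensities.

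At stake is the reported size of the trial's central comparison. A reader would take the intensity coefficient as the effect of intensity, but it would be about half of it. The coefficient would also move with any chance difference between HIGH and LOW sessions at their start, which a pre-to-post comparison would remove.

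**Working it through.** **Inputs from the article.** Purpose, terms and measurement occasions are as set out above. The Sample size section gives a "difference in mean PPTs (25.0 ± 19.7; 42.1 ± 27.2) between two different exercise interventions", with two-sided alpha 0.05, beta 0.20 and "an allocation ratio of 1:1".

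**The plan's own figure.** It is not in dispute and is reproduced only as a check.
- Difference: 42.1 − 25.0 = 17.1.
- Pooled SD: √((19.7² + 27.2²)/2) = √563.97 = 23.75, so d = 17.1/23.75 = 0.720.
- The noncentral t calculation gives 32 per group, 64 in total, with power 0.809. The normal approximation gives 62.
- This agrees with the article: "The calculations revealed that 64 participants would be sufficient". Allowing for 20% loss, 64/0.80 = 80, also as stated.

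**What the intensity coefficient estimates.** Let D_pre and D_post be the mean HIGH-minus-LOW differences before and after exercise. Each completer gives two HIGH rows and two LOW rows, one of each at each time. Intensity is then orthogonal to time, study group and age, and the coefficient is

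b = mean(HIGH rows) − mean(LOW rows) = ½·D_pre + ½·D_post.

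With randomised order and no carryover, E[D_pre] = 0. Write δ for the HIGH-minus-LOW difference in pre-to-post response. Then E[D_post] = δ and E[b] = (0 + δ)/2. With intensity by time added, the interaction coefficient is D_post − D_pre, with expectation δ.

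**Numbers in.** The effect of 10, the imbalance of 4 and the period effect of 6 are assumed values. Fits to noise-free crossover data gave:

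| Case | Listed model, intensity | Interaction |
|---|---|---|
| δ = 10 | (0 + 10)/2 = 5.0 | 10.0 |
| δ = 17.1 | (0 + 17.1)/2 = 8.55 | 17.1 − 0 = 17.1 (by formula) |
| δ = 10, HIGH sessions start 4 higher | (4 + 14)/2 = 9.0 | 14 − 4 = 10.0 |
| δ = 10, period effect of 6 | 5.0 | not run |

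With noise added (150 simulated trials, 64 participants, δ = 10; assumed SDs of 20 for participant, 8 for session and 8 for residual), the listed model averaged 4.70. The interaction averaged 9.81, identical to a change-score analysis.

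**Precision.** With session variance σs², residual variance σe² and n completers:
- Var(b) = (2σs² + σe²)/n, for a target of δ/2.
- Var(interaction) = 4σe²/n, for a target of δ.

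The ratio of the two expected z-values is σe/√(2σs² + σe²). It equals 1 when σs = 0 and falls as σs grows. As an illustration on assumed values (δ = 0.4, σe = 0.4, n = 64; normal approximation):

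| Assumed σs | SE of b | z = 0.2/SE | Power, main effect |
|---|---|---|---|
| 0 | √(0.16/64) = 0.050 | 4.00 | 98% |
| 0.4 | √(0.48/64) = 0.087 | 2.31 | 64% |
| 0.6 | √(0.88/64) = 0.117 | 1.71 | 40% |

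The interaction has SE 2 × 0.4/√64 = 0.10, z = 4.00 and power of about 98% in every row. The article gives none of these variances, so the table shows only how the loss varies.

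**The case against.** The strongest reply is that this regression is not the trial's test of HIGH against LOW. That test is the preceding t-test on within-subject session differences, and the regression runs only if it is significant. This stands. The figures above describe the regression as if it stood alone and are not the power of the trial. But the regression is the model the article offers for evaluating the intensity effect, and the t-test does not supply the missing term. The article does not say whether the t-test uses postexercise values or changes.

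A second reply is that a condensed article may list factors and leave interactions implicit. That is possible. However, this list was written for a stated purpose, and nothing else in the article adds the interaction or a baseline covariate. Followed as written, it gives the wrong quantity.

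A third reply is that exercise-induced hypoalgesia is already a change score. That change is taken around the wall-squat. The Abstract has it assessed before and after the cycling, so the averaging still applies.

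A reader might infer four stronger things that the article does not support:
- *The standard errors are wrong for want of a participant effect.* The article names the fixed effects and is silent on the random part. Assuming ordinary least squares would be a guess.
- *Omitting period biases the intensity effect.* Under 1:1 allocation to the two orders it does not: the coefficient stayed at 5.0 with a period effect of 6.
- *Type I error for intensity is inflated.* If δ = 0, the main effect is also zero in expectation.
- *The trial will report 8.6.* The 17.1 is a planning difference from another study and serves here only to show the scale.

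**Conclusion.** The point holds for the regression as written. With both time points as outcomes and intensity as a main effect only, the coefficient has expectation δ/2. It also carries any chance difference between HIGH and LOW sessions before exercise. The factor of one half needs no variance assumption. It rests on equal expected pre-exercise values (randomised order, no carryover) and on participants completing both sessions, and it would not apply if the outcome were a change score or the postexercise value alone. The two listed levels of time rule out that reading.

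The consequence is an effect size reported at about half its value in a follow-up model. Power may also be lost, by an amount the article does not allow one to state.

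**What to change.** Name the estimand as the HIGH-minus-LOW difference in pre-to-post response. Add intensity by time to the regression and state that this term is the one estimated and tested.

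An alternative is to model the postexercise value on intensity with the same session's pre-exercise value as covariate. It is not equivalent: the interaction fixes the slope on the pre-exercise value at one, whereas the covariate model estimates it and has a different variance. The choice should be made in advance.

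In the same sentence, say that the model accounts for repeated measures within participant and includes period. These are secondary clarifications, not shown errors.

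The cost is a change of wording before analysis. It needs no new data, no change in sample size and only standard mixed-model software.

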### Randomization

2.5

The participants will be enrolled sequentially. After informed consent is obtained, participants will be allocated randomly to one of two groups: INV‐A or INV‐B. Block randomization will be performed with a 1:1 allocation ratio, using the website https://www.sealedenvelope.com/. A table with random numbers generated by the website will be used. Opaque and sealed envelopes containing cards with the name of the intervention group will be used to ensure concealed allocation. A researcher not part of the study will perform the allocation procedure. Owing to the nature of the study trial, blinding of the assessor and participants is not possible.

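### The follow-up regression for HIGH vs LOW names no intensity-by-time interaction; fitted as listed, its intensity coefficient estimates about half of the difference in change

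*Protocol article*

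**What the plan says.** The protocol article, section 2.9 (Statistical analysis), first compares HIGH and LOW with a t-test on within-subject differences between sessions. If that test is significant, "a regression model will be conducted to evaluate the effect of exercise intensity (HIGH vs. LOW) on CS measures". The terms follow: "The fixed effect of time (baseline and postexercise), exercise intensity and study group will be included in the model", and age is added as a covariate. No product of intensity and time is mentioned, and the text does not say which coefficient will be reported as the HIGH vs LOW effect.

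Time is a factor with baseline and postexercise as its levels, so the response is the value at each time and not a change score. Section 2.6 (Data collection) confirms the data layout: "the central pain processing measurements will be performed twice at each session: at baseline; and postexercise". Two sessions therefore give four rows per participant for each measure, two of them from before cycling.

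If the t-test is not significant, section 2.9 turns to a repeated-measures ANOVA with time as the within-subject factor and group as the between-subject factor. Sections 2.4 and 2.5 use group for the order of the sessions (HIGH–LOW or LOW–HIGH), so that ANOVA has no intensity factor.

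**The concern.** Intensity can act only on what is measured after cycling. The HIGH vs LOW question is therefore whether the baseline-to-postexercise change differs between the two sessions, and in a model with both rows that is the intensity-by-time interaction. A model with only main effects forces the HIGH–LOW gap to be the same before and after exercise, and its intensity coefficient estimates that common gap.

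The regression is the only model in section 2.9 that contains both time and intensity, and section 2.9 gives it the task of evaluating intensity. The Discussion (section 6) states the HIGH vs LOW comparison on measures of central sensitization as an aim. If the intensity main effect were reported as the answer, the estimate and its confidence interval for exercise-induced hypoalgesia, temporal summation and conditioned pain modulation would be centred on about half of the intended quantity.

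**Working it through.** **Inputs.** Model terms: section 2.9. Rows: two per session over two sessions, section 2.6. Allocation: "Block randomization will be performed with a 1:1 allocation ratio", section 2.5. Means and SDs: "25.0 ± 19.7; 42.1 ± 27.2", and design values: "α = 0.05, β = 0.20, and an allocation ratio of 1:1", both section 2.8.

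**1. The plan's own figure.** Difference = 42.1 − 25.0 = 17.1. Pooled SD = √[(19.7² + 27.2²)/2] = 23.75. Standardized difference = 17.1/23.75 = 0.72. For two independent groups, the exact t calculation gives 79.7% power at 31 per group and 80.9% at 32, hence 64 in total, and 64/(1 − 0.20) = 80. The stated figures reproduce, and the model point does not enter them.

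**2. What the intensity coefficient estimates.** Let D_base and D_post be the HIGH-minus-LOW differences at baseline and postexercise, and δ the HIGH-minus-LOW difference in change. Baseline precedes cycling, so E[D_base] = 0 and E[D_post] = δ. With complete, balanced rows:

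- main-effects model: coefficient = (D_base + D_post)/2, expectation (0 + δ)/2 = δ/2;
- interaction: D_post − D_base, expectation δ.

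Participant and session terms do not alter this, because in balanced data they leave the intensity contrast unchanged.

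**3. Numerical check.** A least-squares fit to noiseless crossover data (80 participants, four rows each) used δ = 17.1, borrowed from section 2.8 for illustration only, and an assumed LOW change of 5.

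| Model | Intensity | Time | Intensity × time |
|---|---|---|---|
| As listed | 8.55 | 13.55 | – |
| With interaction | 0 | 5 | 17.1 |

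Here 8.55 = 17.1/2, and 13.55 = 5 + 8.55 is the change averaged over both intensities.

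With noise, 300 simulated random-intercept models (64 participants, true δ = 6; assumed SDs 20 for person, 8 for session, 8 for residual) gave a mean intensity coefficient of 2.82 without the interaction and a mean interaction of 5.82 with it. The targets are 3 and 6. The shortfalls of 0.18 are within about two simulation standard errors: √3/√300 = 0.10 and √4/√300 = 0.12. A separate run of 2,000 trials (64 participants, true δ = 5) gave 2.50 and 5.00.

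**4. Power.** Let V be the variance of each of D_base and D_post, and r their correlation. The main-effect estimator has variance V(1 + r)/2 and the interaction 2V(1 − r). The ratio of signal to noise, main effect to interaction, is

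(δ/2)/√[V(1 + r)/2] ÷ δ/√[2V(1 − r)] = √[(1 − r)/(1 + r)].

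The article gives no r. Over an assumed range, and supposing that the interaction test has 80% power with 64 participants:

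| r (assumed) | Ratio | Power of main-effect test |
|---|---|---|
| 0 | 1.00 | 80% |
| 0.3 | 0.73 | 54% |
| 0.5 | 0.58 | 37% |
| 0.7 | 0.42 | 22% |

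The halving in step 2 does not depend on r. The power loss does, and it is nil at r = 0.

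**The case against.** The best defence is that section 2.9 names factors and does not write out a formula. It does not say main effects only, does not exclude an interaction, and does not say which coefficient will be interpreted. The next sentence describes the repeated-measures ANOVA in the same way, naming time and group without their product, although such an ANOVA routinely includes it. The article is condensed, and an analysis plan that is not shown may give the full model. This stands as a limit: the article does not establish that the authors will report a halved effect. It does not dispose of the point, because the article states the model's purpose and lists its terms, and those terms followed literally answer a different question. No other part of section 2.9 supplies the missing contrast.

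A reader might also infer more than the text supports:

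- **That the HIGH vs LOW test is invalid or gives false positives.** The determination of a difference is assigned to the t-test, which this point does not touch. The regression is a conditional follow-up, and its intensity coefficient still has expectation zero when intensity has no effect.
- **That the effect of exercise itself is halved.** The quantity halved is the difference between intensities. The average baseline-to-postexercise change, which bears on the primary aim as worded in the Introduction, is carried by the time term and remains interpretable as an average over both intensities.
- **That the regression will lose power and contradict the t-test.** This rests wholly on the unknown r.
- **That the sample size is wrong on this account.** It is not affected.

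**Conclusion.** The concern holds in a limited form. If the follow-up regression is fitted with only the listed terms to baseline and postexercise rows, its intensity coefficient estimates about half of the HIGH-minus-LOW difference in change. The factor is exactly one half in expectation when all rows are present, the design is balanced and the expected baselines are equal in the two sessions. Chance baseline differences or missing rows move an individual estimate but do not restore the right target. The consequence is for the estimate, its confidence interval and their interpretation; a loss of power is possible but cannot be sized from the article. It should be settled before analysis, because the model as listed does not give the quantity it is meant to evaluate and the correction is nearly free.

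**What to change.** Reword the model sentence in section 2.9, or state the following in the analysis plan. Choose one form:

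- **Both rows:** include time, intensity and intensity-by-time, and name the interaction (the HIGH-minus-LOW difference in baseline-to-postexercise change) as the HIGH vs LOW estimate.
- **Postexercise rows only:** include the same-session baseline as a covariate, so that the intensity coefficient is the effect.

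In either form keep session (period) and a participant effect in the model. The two forms share a target but differ in precision. In the notation above the interaction has variance 2V(1 − r). Postexercise values with no baseline adjustment would have variance V, which equals it only at r = 0.5. The form should therefore be chosen in advance. The intensity main effect from a main-effects model should not be reported as the HIGH vs LOW effect.

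The cost is one sentence. No visit, measurement or sample size changes.
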